## Abstract

**Background:**

Parkinson's disease is a progressive neurological disorder resulting from a degeneration of dopamine producing cells in the substantia nigra. Clinical symptoms typically affect gait pattern and motor performance. Evidence suggests that the use of individual auditory cueing devices may be used effectively for the management of gait and freezing in people with Parkinson's disease. The primary aim of the randomised controlled trial is to evaluate the effect of an individual auditory cueing device on freezing and gait speed in people with Parkinson's disease.

**Methods:**

A prospective multi-centre randomised cross over design trial will be conducted. Forty-seven subjects will be randomised into either Group A or Group B, each with a control and intervention phase. Baseline measurements will be recorded using the Freezing of Gait Questionnaire as the primary outcome measure and 3 secondary outcome measures, the 10 m Walk Test, Timed "Up & Go" Test and the Modified Falls Efficacy Scale. Assessments are taken 3-times over a 3-week period. A follow-up assessment will be completed after three months. A secondary aim of the study is to evaluate the impact of such a device on the quality of life of people with Parkinson's disease using a qualitative methodology.

**Conclusion:**

The Apple iPod-Shuffle™ and similar devices provide a cost effective and an innovative platform for integration of individual auditory cueing devices into clinical, social and home environments and are shown to have immediate effect on gait, with improvements in walking speed, stride length and freezing. It is evident that individual auditory cueing devices are of benefit to people with Parkinson's disease and the aim of this randomised controlled trial is to maximise the benefits by allowing the individual to use devices in both a clinical and social setting, with minimal disruption to their daily routine.

**Trial registration:**

The protocol for this study is registered with the US NIH Clinical Trials Registry (NCT00727467).

## Background

Parkinson's disease (PD) is a progressive neurological disorder resulting from a degeneration of dopamine producing cells in the substantia nigra [1]. Clinical symptoms such as tremor, rigidity, bradykinesia, hypokinesia and postural instability classically affect gait pattern and motor performance [2,3]. Typically, people who present with PD have an inability to maintain internal gait rhythm [4], resulting in an abnormal gait pattern including short shuffling steps, decreased arm-swing [5], freezing [4-6], festination [7], decreased stride length [8,9], reduced walking speed and increased cadence and double stance time [2,4].

Rubenstein and colleagues [10] advocate the use of cueing devices in physiotherapy, as such devices have demonstrated an immediate effect on gait, with improvements in walking speed, stride length and cadence [8,9]. Cueing is defined as using external temporal or spatial stimuli to facilitate movement, gait initiation and continuation [6], and may be used effectively in a home environment for the management of gait and freezing in individuals with PD [11]. The RESCUE trial [11] demonstrated the efficacy of the use of individual auditory cueing devices (IACD). However, the technology used in this protocol is not commercially available to date. Therefore, in this article we describe a protocol to evaluate the effect of a widely available IACD – the Apple iPod-shuffle™ (iPod) on freezing and gait speed.

The iPod is an off-the-shelf, low cost MP3 player, combining the latest auditory technology with an aesthetically appealing, built-in clip design and user-friendly interface. The iPod can be attached to any item of clothing without being conspicuous and the in-ear headphones have excellent sound quality and fit comfortably and securely in the ear.

It is not exactly clear how AC improves gait, however McIntosh and colleagues [12] hypothesise that an external AC compensates for the defective internal rhythm of the basal ganglia. Research also suggests that AC may provide a rhythmic training mechanism because the effects of AC on the individual remained even after cues were removed [11-14]. In the study by McIntosh and colleagues [12], people with PD who listened to music with an overlaid AC whilst exercising showed lasting gait improvements, compared to those who exercised without an AC. In a similar study [14], individuals with PD who listened to music with an AC on a daily basis for a month without gait training showed significant improvements in gait velocity and step length.

### Background Work

A systematic review of randomised control trials (RCTs) was explored [15]. The review demonstrated that significant improvements in walking speed, stride length and cadence were evident in the 'experimental' groups when AC was used as an intervention [16,17]. The primary gait deficiency in people with PD has been described as an inability to generate sufficient amplitude of movement [18]; therefore cues should be aimed at increasing step amplitude [18] and enlarging stride length to have a maximum impact on normalising gait patterns of people with PD [19].

The review [15] also suggested that by increasing the auditory cueing (AC) frequency by +10% to 20% of individuals with PD natural step frequency, there is an immediate effect on walking speed and stride length [19-21]. However, the effects of increased stride length have been reported as inconsistent in people with PD who freeze [22]. Preliminary findings on people with PD who freeze indicate that lowering the AC frequency by 10% (-10%) of the individuals self-selected walking speed can help to improve their stride length [22,23]. Therefore the investigators calculated and pre-loaded 100 baseline frequencies (less 10%) in the sound of a metronome beat in an MP3 format (30 – 130 BPM) onto a DVD-R [24].

A user manual was created with a set of instructions that gives each physiotherapist a step-by-step guide on how to calculate the correct beat for their participants and how to successfully upload this beat onto the iPod. In addition physiotherapists in participating centres attended a training session on how to complete the tasks. A pack including the DVD-R, user manual, information leaflet and consent form was sent to participating centres. Recruitment is due to commence in January 2009.

In addition, other authors have found that a single task attention strategy such as walking in a straight line, with a single auditory cue, resulted in significant normalisation of gait parameters with improvements in walking speed, step amplitude, and step frequency [20,23,25-30]. The results of a recent study demonstrated a significant increase of 0.7 m in mean step length with AC compared to walking with no cues in a dual motor task, and significant increases in step amplitude with rhythmic auditory cueing during dual and multi-task performances in the home [23].

Using this body of evidence, the investigators developed a protocol to evaluate the impact of a low cost, widely available individual auditory cueing device on freezing and gait speed in people with Parkinson's disease.

### Aims and Objectives of the Study

The primary aim of the study is to evaluate the effect of an IACD i.e. Apple iPod-shuffle™, on freezing and gait speed in people with a diagnosis of PD through the implementation of a randomised controlled trial. A secondary aim of the study is to evaluate the impact of such a device on the quality of life of people with PD through the administration of a self-report questionnaire. The IACD will be pre-loaded with an individualised auditory cueing frequency (metronome sound) matched to the walking speed of the person.

## Methods

### Study Design

A randomised cross over design will be used. Forty-seven subjects will be randomised into either Group A or Group B using sealed, computer generated random numbers.

### Ethical Considerations

The study has obtained ethical approval from Trinity College, University of Dublin Research Ethics Committee (3/7/08).

### Intervention

On Days 1–8 of the trial, the participants in Group A and Group B will be given the iPod, loaded with podcasts. During this period they will familiarise themselves with the functionality of the device i.e. turning the device on and off, increasing and decreasing the volume and inserting the earphones into the ear. They will be instructed to use the device only when sitting at home, and also instructed that the device should not be turned on when walking or performing any mobility related or daily tasks. Investigators will schedule a phone call to check the device is being used properly and that the participant is not having any problems.

On Days 8–15, participants in Group A will be allocated to the 'intervention' phase. Each participant will be given an iPod containing an auditory cue in the form of a continuous metronome beat, individualised to the person's walking frequency (less 10%). Participants will be instructed to listen to the cueing when they are performing any mobility related tasks. They will be encouraged to listen to the rhythmical cue and to try to match their heel strike with the beat of the metronome sound on the device. During this time period, participants in Group B will be allocated to the 'control' phase. Participants will be provided with the iPod shuffle containing no music or metronome beat. Participants will be instructed to continue using the device in a similar manner to that of the first week. On Days 15–23, participants in Group A will be allocated to the 'control' phase and participants in Group B will be allocated to the 'intervention' phase. The progression from screening and enrollment to randomisation is illustrated in Figure legend 1.

**Figure 1 F1:**
[figure not shown]
Outline of RCT study design.

### Outcome Measures

Assessments will be taken 3 times over the 3-week period on days 8, 15 and 23. A follow-up assessment will be completed after 3 months. The primary SOM in this study is the Freezing of Gait Questionnaire (FOGQ) [31]. The severity of freezing of gait is most accurately assessed by the FOGQ. The questionnaire focuses solely on freezing and does not include items relating to falling or festination. The FOGQ has been shown to be both valid and reliable as an outcome measure in people with PD [31].

Secondary outcomes will also be utilised including the 10MWT [32], TUG [33] and the MFES [34]. The 10MWT [32] has been found to be valid and reliable in measuring speed in people with PD and will be used as a measure of gait speed during the different time-points in the study. The TUG [33,35,36] has been used as a tool for measuring basic mobility performance and has been proven to be both valid and reliable in people with PD [35]. The MFES [34], unlike the Falls Efficacy Scale (FES) [34,37], assesses outdoor activities as well as indoor activities and demonstrates greater internal test-retest reliability then the original FES. The MFSE will be used to evaluate any change which may occur in an individuals falling pattern due to auditory cueing.

In addition, the impact of the AC device on the individual and their quality of life with be explored using a semi-structured interview. This interview will be conducted by a person unknown to the participant. All interviews will be audio-recorded.

### Participant Selection

The potential participants involved in this study will be volunteers recruited from the Parkinson's Association of Ireland, as well as suitable medically stable candidates recommended by a consultant and/or physiotherapists from a number of hospitals and day centres in Ireland.

### Inclusion/Exclusion criteria

Individuals will be admitted to the study if they present with a formal diagnosis of PD and are recommended for participation to the study by a consultant and/or physiotherapist. Participants on a stable medication regime who freeze at least once a week (minimum score of 2 on item 3 of the FOGQ) and who freeze for at least 2 seconds (minimum score of 1 on item 4 of FOGQ).

Participants will be excluded if they are attending physiotherapy at the time of recruitment. Such participants may demonstrate an improvement in gait pattern following physiotherapy intervention, which may not be attributable to the AC device. Individuals who are unable to use the IACD, who cannot hear the auditory cues and anyone unwilling to provide written informed consent will be excluded. Additionally individuals with acute co-morbidities influencing mobility will also be excluded. Potential participants with a cognitive impairment (< 24 MMSE) or with long/unpredictable "off" periods making stable testing difficult will also be excluded.

### Recruitment

The nominated physiotherapist in each participating centre will be responsible for assessing eligibility for inclusion into the study and also for obtaining informed consent from the patient. Following identification of suitable participants the aims of the project, including the role of the participant will be outlined and any questions answered by the physiotherapist. The person with PD will receive an information brochure in advance of being asked to give written informed consent. Participants will have seven days between receipt of the information brochure and being requested to give written consent. Following the 7-day interval, the physiotherapist will answer or clarify any further questions that arise and the participant will be requested to sign a consent form. If they are unwilling to give written consent, they will be excluded from the study. If they decide to partake in the study, participants will be advised that they can withdraw from the study at any time and it will not interfere with their routine rehabilitation programme. Participants will be allocated a reference code. Names and other details that may identify the participants will be removed.

### Randomisation

To minimise the possibility of recruitment bias, a person independent of the recruitment process will complete random group allocation. Computer generated random numbers will be kept in pre-sealed envelopes in a locked drawer in the Department of Physiotherapy. Allocation will be revealed after recruitment by a telephone call from the physiotherapist to an independent person, who will open the next envelope in the sequence and give the randomisation information to the physiotherapist. Each envelope will only be opened on enrolment of an eligible participant. After allocation has been revealed, the appropriate intervention will be organised by the physiotherapists carrying out the study.

### Power

Sample size is based on power analysis. A sample size calculation was performed for the two quantitative measures, namely the TUG and 10MWT. Power calculations indicate that a total of 47 participants are needed in order to detect with 80% power a difference of 20% between the groups at significance of level of 5%. It is anticipated that it will take 6 months to recruit the required number of participants.

### Analysis

All data will be collected on paper and the records will be stored by registration number in a secure cabinet. Anonymised data will be transferred to a computer database and secured using a password. An independent researcher will cross check all entries. Appropriate statistical tests will be carried out on the data using MINITAB Release 13.1.

The purpose of the statistical analysis is to test the hypothesis that there will be a statistically significant difference in freezing, gait speed and number of falls from baseline to post-intervention assessment. Firstly, the participants' demographic details and primary and secondary outcome measure scores will be compared in the two groups at baseline. If necessary, adjustments for baseline variables will be made using analysis of covariance. Analyses will be carried out to examine the difference between the groups with respect to the change in the FOGQ score from baseline to post-intervention assessment. Secondary outcomes will be compared between the two groups using Student's t-test or the Wilcoxon rank sum test for ordinal data. Descriptive statistics will also be used to represent demographic data.

All interviews will be transcribed verbatim and examined in terms of themes according to the method devised by Miles and Hubberman [39]. Firstly, participants responses to each question will be transferred into a Microsoft excel document to facilitate analysis. Following analysis of the responses to each question, a coding system will be developed in order to facilitate the identification of recurrent responses. Three researchers will be provided with the responses to all of the questions in an unencoded format; thereafter they will independently code the responses sequentially using the predefined codes. Any coding disagreements will be resolved through discussion.

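### Baseline adjustment of the between-group comparison depends on an observed baseline difference, which costs precision and leaves the model open until data are seen

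*Protocol article*

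**What the plan says.** The Analysis section sets out a sequence. Demographic details are compared first, and "primary and secondary outcome measure scores will be compared in the two groups at baseline". The next sentence reads: "If necessary, adjustments for baseline variables will be made using analysis of covariance". The FOGQ, the primary outcome, is then to be analysed as "the difference between the groups with respect to the change in the FOGQ score from baseline to post-intervention assessment". For the rest, "Secondary outcomes will be compared between the two groups using Student's t-test or the Wilcoxon rank sum test for ordinal data".

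The article does not say what would make adjustment necessary or which baseline variables would enter. Nor does it say whether secondary outcomes are compared as changes or as raw follow-up scores.

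Three facts from other sections matter:
- Study Design: "A randomised cross over design will be used".
- Outcome Measures: "Assessments will be taken 3 times over the 3-week period on days 8, 15 and 23". The Intervention section puts both groups through the same familiarisation week up to Day 8, so the Day 8 scores precede the split. The article does not label Day 8 as baseline, but it is the only scheduled assessment before the phases diverge.
- Randomisation: allocation uses computer-generated random numbers held in sealed envelopes.

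**The concern.** With concealed random allocation, any difference between the groups at Day 8 is chance. Looking at its size does not tell the analyst whether adjustment is worthwhile. What matters is how strongly the Day 8 value predicts the later value, and that holds whether or not the groups happen to look alike.

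Three things are at stake:
- **Precision.** In most trials run under this rule no imbalance would be called, and the less efficient default would be reported although the covariate had been collected.
- **Calibration.** When an imbalance is present but judged too small to act on, the unadjusted analysis no longer has its nominal error rate for that data set.
- **Discretion.** With no criterion for need, whoever analyses the data can see both results before deciding which one the rule calls for.

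**Working it through.** **The plan's own figure.** The Power section says: "Power calculations indicate that a total of 47 participants are needed". It rests on the TUG and 10MWT, a 20% difference, 80% power and 5% significance, with no SD. It can be neither confirmed nor refuted. Read as a two-sided two-group comparison with 23.5 per group, it implies a coefficient of variation of 0.20 / (2.80 × √(2/23.5)) = 0.20/0.817 = 0.245. Nothing below depends on this beyond group sizes of 24 and 23.

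**Step 1: variance of the between-group contrast.** Assume equal variances at Day 8 and follow-up, with correlation r between them. The article gives no r, so a range is shown. In units of the outcome variance:
- raw post score: 1
- change score: 2(1 − r)
- ANCOVA: 1 − r²

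ANCOVA against change score is (1 − r²)/(2(1 − r)) = (1 + r)/2. ANCOVA against raw post score is 1 − r².

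| r | ANCOVA / change | ANCOVA / raw post |
|---|---|---|
| 0.5 | 0.75 | 0.75 |
| 0.7 | 0.85 | 0.51 |
| 0.9 | 0.95 | 0.19 |

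The first ratio is the one for the FOGQ. The second applies only to an outcome compared as a raw follow-up score.

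**Step 2: what this is worth for a change-score outcome.** At r = 0.7 the difference detectable with 80% power, 24 against 23, is 0.835 × √0.60 = 0.65 SD for the change score and 0.835 × √0.51 = 0.60 SD for ANCOVA. If the change-score analysis had exactly 80% power (hypothetical; no FOGQ power is stated), ANCOVA would have Φ(2.80/√0.85 − 1.96) = 86.0%. The same formula gives 89.9% at r = 0.5 and 82.0% at r = 0.9.

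**Step 3: what the conditional rule recovers.** A simulation (24 against 23, 40,000 runs) used ANCOVA only when a baseline test gave p < 0.05. That threshold is an assumption. It triggers in about 5% of trials.

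| r | Change score | Conditional rule | Always ANCOVA |
|---|---|---|---|
| 0.5 | 78.3% | 79.2% | 87.8% |
| 0.7 | 78.3% | 78.8% | 83.7% |
| 0.9 | 78.1% | 78.1% | 79.4% |

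The rule recovers little or none of the gain.

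**Step 4: error under the null.**
- *Averaged over all imbalances, rule applied mechanically:* with r from 0.3 to 0.9, type I error is 4.2% to 4.8% with a p < 0.05 trigger and 3.3% to 4.7% with p < 0.20. This is slightly conservative.
- *Given an observed imbalance:* suppose the baseline difference is 1.9 standard errors, just short of a 5% trigger. The change-score statistic then has mean of size 1.9 × √((1 − r)/2) and SD √((1 + r)/2). At r = 0.7 these are 0.736 and 0.922, so the chance of exceeding 1.96 in either direction is about 9%. At r = 0.5 they are 0.95 and 0.866, giving about 12%.
- *If the analyst reports the more favourable of change score and ANCOVA:* about 8.0% at r = 0.3, falling to 5.9% at r = 0.9.

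**Step 5: a within-patient crossover contrast.** Here the treatment effect comes from Day 15 minus Day 23. If Day 8 correlates with them at r₁ and r₂, and they correlate with each other at r₁₂, adjusting for Day 8 removes (r₁ − r₂)²/(2(1 − r₁₂)) of the variance. This is zero when r₁ = r₂. With r₁₂ = 0.7, the pair 0.7 and 0.6 gives 0.01/0.60 = 1.7%, and 0.7 and 0.49 gives 0.0441/0.60 = 7.4% (all assumed).

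**The case against.** Most of the case on the other side concerns reach, and much of it stands.

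- **The article is a condensed text.** Covariate lists and thresholds often sit in a fuller document, so their absence is no fault. But the article does state the rule that adjustment follows from a baseline comparison, and that rule is the problem.
- **The FOGQ default already uses baseline.** This stands. A reader might infer from the 1 − r² column that the primary analysis loses half its precision at r = 0.7. The Analysis section specifies a change score, so the loss there is 15%.
- **No baseline significance test is stated.** This stands. A reader might compute 1 − 0.95⁴ = 18.5% as the chance of at least one spurious imbalance among four outcomes. That needs 5% tests and independent outcomes, and the article states neither. Under a common correlation of 0.3, 0.5 or 0.7 the figure is about 17%, 16% or 13%. Nor does it measure harm, since a false flag leads to the adjusted model.
- **A two-stage rule need not inflate error.** This stands for the overall rate. A reader might infer general inflation; Step 4 shows the opposite unless results are picked.
- **The trial is a crossover.** This stands. In a within-patient analysis a single Day 8 value largely cancels. The gains belong to the between-group comparison that the Analysis section describes. Whether that comparison suits the design is a separate and larger question.
- **Adjustment is not entirely free.** This stands. Requiring a covariate displaces the Wilcoxon test planned for ordinal data, so a replacement has to be named.

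**Conclusion.** The point holds in limited form. The stated rule lets a chance baseline difference decide the model, and its default is less precise than adjusting in every case. For the FOGQ between-group comparison, fixed ANCOVA would lower variance by about 25% at r = 0.5, 15% at r = 0.7 and 5% at r = 0.9. At r = 0.7 that is 5 to 6 points of power (78.3% to 83.7% simulated; 80% to 86.0% by normal approximation). Secondary outcomes gain more only if they are compared as raw post scores and r exceeds 0.5.

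The harms are lost power, miscalibrated error given an observed imbalance (about 9% at r = 0.7 for a 1.9 standard error difference left unadjusted), and open choice of model. Inflation of the overall type I error by the rule itself is not among them.

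These sizes rest on an assumed correlation, equal variances and approximate normality. That the rule is badly fixed does not depend on them.

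**What to change.** Replace the conditional sentence with wording such as: *Each between-group comparison of an outcome includes that outcome's own Day 8 value as a covariate, whatever the baseline comparison shows. Where scores are ordinal and a rank test would have been used, a rank-based analysis of covariance (for example Quade's method) is used instead. Baseline characteristics are tabulated descriptively and do not determine the model.*

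The wording should say that Day 8 is the baseline and which later assessment is compared. Group B does not start cueing until Day 15, so its post-intervention point is not the same as Group A's.

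Do not extend the instruction to a within-patient crossover model, where the Day 8 covariate adds little or nothing.

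The cost is one degree of freedom and a named method for ordinal scores. No new data are needed, and the article already intends to have analysis of covariance available.

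### The primary analysis compares two sequence groups that both receive the device, at a post-intervention visit tied to no study day; read plainly, the device effect cancels.

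*Protocol article*

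**What the plan says.** The Study Design section states: "A randomised cross over design will be used". The abstract says that participants are "randomised into either Group A or Group B, each with a control and intervention phase", so the two groups are treatment sequences and not a treated arm and a control arm.

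The Intervention section gives the order:
- First period: "On Days 8–15, participants in Group A will be allocated to the 'intervention' phase", and "During this time period, participants in Group B will be allocated to the 'control' phase".
- Second period: Group A moves to control and "participants in Group B will be allocated to the 'intervention' phase". No washout between the phases is described.

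The Outcome Measures section places assessments on Days 8, 15 and 23, with a follow-up at three months.

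For the primary outcome, the Analysis section will "examine the difference between the groups with respect to the change in the FOGQ score from baseline to post-intervention assessment". It compares secondary outcomes between the two groups by Student's t-test or the "Wilcoxon rank sum test for ordinal data", naming no visit and no phase. Its hypothesis concerns a difference from baseline to post-intervention, without mention of the control phase.

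**The concern.** The stated contrast belongs to a parallel-group trial, where only one group is treated. Here each group has its own post-intervention visit: Day 15 for A and Day 23 for B. Comparing the two groups at those visits compares people who have just used the device with other people who have just used the device.

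An analyst following the sentence literally could report no effect for a device that works. The same analyst could report a significant difference that reflects only practice or drift over one extra week. Because the sentence names no study day, another analyst could choose Day 15 or Day 23 for everyone and obtain a different estimate from the same data. This is the primary outcome, and the sentence on secondary outcomes leaves the same gap.

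**Working it through.** **Inputs from the protocol article.** 47 participants (taken as 24 and 23); A treated on Days 8–15 and B on Days 15–23; visits on Days 8, 15 and 23. Day 8 is taken as baseline.

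**The plan's own figure.** The Power section gives 47 for 80% power, a 20% difference and a 5% level, based on TUG and 10MWT. It states no SD or correlation, so 47 can be neither reproduced nor refuted. Solving back for a two-sided, two-group comparison gives SD = 0.20 × √(23.5/2) / (1.960 + 0.842) = 24.5% of the mean. The point below does not depend on this.

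**Expected values.** Let τ be the device effect, π1 and π2 the period effects at Days 15 and 23 relative to Day 8, and λ the carry-over into Group A's control phase.

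| Reading of post-intervention | Change in A | Change in B | A minus B |
|---|---|---|---|
| Own visit (A Day 15, B Day 23) | τ + π1 | τ + π2 | π1 − π2 |
| Own visit, B measured from Day 15 | τ + π1 | τ + π2 − π1 | 2π1 − π2 |
| Day 23 for both | λ + π2 | τ + π2 | λ − τ |
| Day 15 for both | τ + π1 | π1 | τ |

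In the first two rows τ disappears, whatever the SD, correlation or effect size. Carry-over does not restore it, since neither group has been treated before its own intervention phase.

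The crossover contrast is ½[(A15 − A23) − (B15 − B23)] = ½[(τ + π1 − π2 − λ) − (π1 − π2 − τ)] = τ − λ/2.

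**Size.** Assumed: unit SD, within-person correlation ρ = 0.7, τ = 0.5 SD, two-sided 5% level.
- SE of a between-group difference in change: √[2(1 − ρ)(1/24 + 1/23)] = √(0.6 × 0.0851) = 0.226.
- Own-visit reading, no drift: expectation 0, rejection 5%.
- Own-visit reading, 0.2 SD drift in the second week: expectation −0.20, ratio 0.2/0.226 = 0.89, rejection about 14%. This is the same for τ = 0.5 and τ = 0.
- Day 23 for both: −0.50 with no carry-over, −0.25 with half carried over, 0 with full carry-over.
- Day 15 change score: 0.5/0.226 = 2.21, power about 58% (38–39% at ρ = 0.5).
- Day 15 ANCOVA on Day 8: SE = √[(1 − 0.49) × 0.0851] = 0.208, power about 65% (48–49% at ρ = 0.5).
- Crossover contrast, λ = 0: SE = 0.226/2 = 0.113, ratio 4.42, power about 99% (92% at ρ = 0.5).
- Crossover contrast with carry-over: 0.5 − 0.25/2 = 0.375 SD at half, and 0.5 − 0.5/2 = 0.25 SD at full, where power falls to about 58%.

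**Second check by simulation** (4,000 runs, ρ = 0.6, τ = −0.8 SD, no drift or carry-over). Own-visit reading: mean 0.00, rejection 5.8%. Day 15 change: mean −0.80, power 85%. Crossover: mean −0.80, power about 100%. With τ = 0, π1 = −0.1 and π2 = −0.5, the own-visit reading averaged +0.40 and rejected in 32% of runs, while the crossover contrast stayed at 0.00 and 5%.

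**The case against.** The strongest reply is that the sentence is ambiguous rather than wrong. No study day is attached to the post-intervention assessment, and the Intervention section sets intervention in A against control in B on Days 8–15, so a Day 15 comparison may have been intended. This stands in part. A reader might infer that the planned comparison can never estimate the device effect; the document does not support that, because the Day 15 reading does estimate it. But Day 15 ends Group B's control phase, so the wording does not describe that reading.

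Four other inferences go too far:
- **The t-test and rank sum test are the wrong tests.** They are not at fault; both are valid between sequences on Day 15 minus Day 23 differences. What is missing is the quantity they compare.
- **The 47 participants rely on crossover efficiency.** The Power section shows no such thing. It speaks of a difference between groups and gives no correlation.
- **Day 23 for both groups always gives the wrong sign.** That requires little carry-over; with full carry-over the contrast is zero.
- **Leaving out period 2 is plainly a loss.** The Background cites evidence that cueing benefits outlast the cues. With full carry-over at the assumed 0.5 SD, Day 15 ANCOVA (65%) has more power than the crossover contrast (58%), and no bias from carry-over. At an assumed 0.8 SD and correlation 0.7, even the Day 15 change score has about 93% power.

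An article may leave detail to a fuller plan. That does not answer the point here, because the article does state the primary contrast and that contrast does not fit its own design.

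**Conclusion.** The point holds and needs correcting before analysis. On the plain reading, the primary comparison has expectation π1 − π2 and contains no device effect. That result is algebraic. It assumes only additive effects and that each group is measured after its own intervention phase.

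Depending on the visit chosen, the same sentence yields zero plus drift, a reversed or shrunken effect, or the correct effect. The rejection rates and powers rest on assumed effects, correlations and drifts that the document does not give; they illustrate the size and are not needed for the conclusion. For the secondary outcomes the finding is narrower: visit and phase contrast are not stated.

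**What to change.** Replace the primary-analysis sentence with an explicit intervention-phase versus control-phase contrast, and use it for FOGQ, 10MWT, TUG and MFES. Either form will do:
- a model of the Day 15 and Day 23 values with fixed effects for treatment, period and sequence and a random participant effect; or
- a two-sample t-test or rank sum test between sequences on Day 15 minus Day 23 differences, with the estimated difference halved.

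Pre-specify, as companion or sensitivity analysis, the comparison of A with B at Day 15 by ANCOVA on the Day 8 value. It is free of carry-over because nobody has used the cue before Day 8. State that carry-over attenuates the crossover estimate (expectation τ − λ/2). Reword the hypothesis as intervention phase versus control phase.

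The cost is a rewritten paragraph and no new data. The downside is that the Day 15 comparison has less power when there is no carry-over: about 58% as a change score, or 65% with ANCOVA, against 99% for the crossover contrast at the assumed 0.5 SD and correlation 0.7.
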